## Abstract

**Background:**

Cutaneous Leishmaniasis is a worldwide disease, endemic in 88 countries, that has shown an increasing incidence over the last two decades. So far, pentavalent antimony compounds have been considered the treatment of choice, with a percentage of cure of about 85%. However, the high efficacy of these drugs is counteracted by their many disadvantages and adverse events. Previous studies have shown nitric oxide to be a potential alternative treatment when administered topically with no serious adverse events. However, due to the unstable nitric oxide release, the topical donors needed to be applied frequently, making the adherence to the treatment difficult. The electrospinning technique has allowed the production of a multilayer transdermal patch that produces a continuous and stable nitric oxide release. The main objective of this study is to evaluate this novel nitric oxide topical donor for the treatment of cutaneous leishmaniasis.

**Methods and design:**

A double-blind, randomized, double-masked, placebo-controlled clinical trial, including 620 patients from endemic areas for Leishmaniasis in Colombia was designed to investigate whether this patch is as effective as meglumine antimoniate for the treatment of cutaneous leishmaniasis but with less adverse events. Subjects with ulcers characteristic of cutaneous leishmaniasis will be medically evaluated and laboratory tests and parasitological confirmation performed. After checking the inclusion/exclusion criteria, the patients will be randomly assigned to one of two groups. During 20 days Group 1 will receive simultaneously meglumine antimoniate and placebo of nitric oxide patches while Group 2 will receive placebo of meglumine antimoniate and active nitric oxide patches. During the treatment visits, the medications will be daily administered and the presence of adverse events assessed. During the follow-up, the research group will visit the patients at days 21, 45, 90 and 180. The healing process of the ulcer, the health of the participants, recidivisms and/or reinfection will also be assessed. The evolution of the ulcers will be photographically registered. In case that the effectiveness of the patches is demonstrated, a novel and safe therapeutic alternative for one of the most important public health problems in many countries will be available to patients.

## Background

Cutaneous Leishmaniasis (CL) is a worldwide disease that is endemic in 88 countries [1]. It is estimated that 1.5 million people suffer from CL annually and that more than 350 million are at risk of contracting the infection [2-4]. In America, 60,000 new cases of CL are reported annually [5], being endemic in 20 of its 22 countries and in 2 islands of the Caribbean [2]. Currently, CL has affected more than 500 U.S. Army soldiers serving in Iraq [6]. In the Andean region, the incidence of Leishmaniasis has been increasing dramatically over the last two decades; reaching more than 14,000 cases per year from 1996–98 [7]. In Colombia 6,500 cases have been reported [8]. The increase in the reported cases of CL in Colombia has been related to factors such as migration, deforestation, the multiplication of illicit plantations, the armed political conflict and the behavioral changes of the vector. The main strains of *Leishmania *in Colombia are *L. panamensis*, *L. brazilensis*, *L. infantum *and *L. guyanensis*, which are distributed throughout the entire national territory, predominantly in the rural areas [9]. CL is caused by intracellular protozoan parasites of the genus *Leishmania *[1] and is transmitted to humans through the bite of a small percentage of the species of phlebotomus and lutzomyia sandflies classified to date [9]. In the digestive system of the sandflies, this dimorphic parasite presents an extracellular flagellated form called a promastigote, which upon its release in the host blood, is phagocyted by the macrophage, losing its flagella and turning into an amastigote [10]. Dogs, rodents and didelphidae are the natural hosts of the parasite while man is an incidental host [11]. This zoonosis has suffered an interesting urbanization phenomenon, changing from an eminent rural entity affecting mainly men of an active age, to a disease that is affecting all people, especially children [8,12]. The characteristic lesions of this disease are ulcers that heal spontaneously over a period of three months to a year, depending on the isolate, and that leave a flat, atrophic and depigmented scar [13-15]. The CL, especially the one produced by *L. brazilensis *can evolve into mucocutaneous Leishmaniasis (MCL), which has a worse prognosis owing to the deforming character of its lesions [16]. The spontaneous cure of these lesions allows for the acquisition of partial resistance to reinfection, which could explain the higher pathogenicity observed in the children and young adult population [12]. Previous studies have shown a higher incidence of CL and a poor response to treatment in the children population [17]. The program of epidemiological vigilance in Colombia requires that the probable cases of CL (identified by ulcer features and by the patient's origin) be confirmed by microscopic direct examination of a secession sample obtained from the ulcer, if these are negative, by biopsy of the wound. Once confirmed, the cases must be notified to the Local Health Secretary using clinical-epidemiological records. This institution, in charge of the epidemiological vigilance, studies the sources of transmission and distributes the medication to the people affected. Currently, various aspects are considered when treating CL, among which, the risk of developing MCL, the grade, localization, number, size, evolution and persistence of the lesions, are the most important [18]. For more than 60 years, the pentavalent antimony compounds: sodium stibogluconate, (Pentostan^®^, produced by Glaxo-Wellcome) and meglumine antimoniate, (Glucantime^®^, produced by Sanofi-Aventis) have been considered the treatments of choice for this disease [19]. Studies made in Colombia reported a percentage of cure of 85%, using meglumine antimoniate [20,21]. Despite the efficacy of these drugs is high, they present many disadvantages such as parenteral administration, and, reversible secondary effects such as nausea, vomiting, muscular and abdominal pain, cardiac problems, a rise in the concentration of hepatic aminotransferases, and chemical pancreatitis [22,23]. Additionally, the adherence to the treatment is affected by its duration (several weeks) and its availability by the restriction in its distribution. Therapeutic alternatives of second line have been proposed; amphotericin B and pentamidine have been used with excellent results, nevertheless their high cost, little availability, the necessity to hospitalize the patients for their administration and the severity of their secondary effects have limited their use [23,24]. In the last decade new treatments for CL have been developed, using oral agents such as mefloquine, itraconazole, miltefosine, paromomycin, ketoconazole, allopurinol and dapsone, however, they have not shown enough evidence of their effectiveness [19,21,25,26]. In an effort to develop a topical treatment for CL, paromomycin has been used in different preparations. However, healing rates achieved with this medication have not been higher than conventional treatments, even when compared with placebo [27,28]. In several studies, *in vitro *and *in vivo*, it has been demonstrated that nitric oxide (NO) is effective to eliminate various strains of *Leishmania *in its amastigote form [29-35]. The production of NO from the oxidation of L-arginine caused by the inducible nitric oxide synthase (iNOS) constitutes one of the most important defense mechanisms of the macrophages [36], in which two oxidative forms of defense against *Leishmania *have been identified. During the first phase of infection, in response to the phagocytosis process, some promastigotes are eliminated due to the release of the superoxide ion, a process which is catalyzed by the NADPH oxidase [29]. Those promastigotes that survive this defense mechanism evolve into amastigotes, activating the production of IL-12 in the macrophages and promoting the presentation of the antigens of *Leishmania *[29] to the T helpers 1 lymphocytes that enhance the cytotoxic activities of the macrophages toward the intracellular parasites via the interferon gamma (INFγ) and the tumor necrosis factor alpha (TNFα) by promoting the production of NO catalyzed by iNOS [31-33]. A recent study shows a higher activity of iNOS in the macrophages of subjects infected with CL, suggesting a vital role of NO in the immunological activity against *Leishmania *[34]. In Studies with rodents resistant to *Leishmania *infection (C57BL/6), where *L. major, L. chagasi *or *L. donovani *were inoculated, the application of iNOS inhibitors like N^G^-monomethyl-L-arginine (L-NMMA) caused a higher rate of survival and virulence of the parasites in macrophages [33,35,37,38]. After inoculating *L. major *in mice with the genetic susceptibility to develop infections with *Leishmania *(BALB/C), no activity of iNOS was observed. However, the application of IL-12, was able to control the infection by activating iNOS [31]. In humans, several clinical trials have been realized with topical treatments containing NO donors [39,40]. In Ecuador, our group developed and tested a NO generating topical cream with S-nitroso-N-acetylpenicillamine (SNAP), evidencing a beneficial effect in the management of this type of ulcers with no reports of any serious adverse event.

Nevertheless, due to the unstable nitric oxide release, the cream had to be applied frequently (4 times a day) making the adherence to the treatment difficult [39]. In Syria, another group used potassium nitrate acidified with salicylic acid and ascorbic acid for the topical treatment of *L. tropica *[40]. *In vitro*, this NO generating mixture destroyed the amastigotes and promastigotes of *Leishmania*; however, *in vivo*, the study of 40 patients presented inconsistent results, reducing the size of the ulcer in 28% of the subjects and healing only 12%. The discrepancy in these results is believed to be due to the technique used to obtain the NO. The acidification of nitrite produces an instant blast of NO, but its release is not maintained over a long period of time[40]. The difficulty of controlling the liberation of NO has created the necessity of looking for new techniques to regulate its release. The nanofiber polymers produced by the electrospinning technique have been studied in order to guarantee the constant release of pharmaceuticals on the lesion. In the electrospinning process, a high voltage is used to create an electrically charged jet of polymer solution, which dries and solidifies to leave behind a dry polymer fiber [41]. As this jet travels through the air, the solvent evaporates leaving behind a charged fiber that can be electrically deflected and collected on a metal screen [42,43]. Fibers with a variety of cross sectional shapes and sizes are produced from different polymers. With this technique, the encapsulation or entrapment of several pharmaceuticals, enzymes and proteins has been successful. In a previous study, nanofiber patches were successfully used as releasing vehicles of tetracycline hydrochloride. The release of tetracycline was constant for a period of 5 days [41,43]. Using the same model, a multilayer transdermal patch has been produced, in which nitrite is bound to an ion exchange resin (DOWEX) and electrospun into a polyurethane nanofibers layer. A solution containing Waterlock^® ^superabsorbent and polyurethane is electrospun on top of the nitrite-DOWEX layer. The ascorbic acid entrapped in the polyurethane solution is electrospun onto a third layer, with another layer of Waterlock^® ^superabsorbent and polyurethane as the fourth and final one. Upon hydration, this Nitric Oxide Releasing Patch (NOP) produces a stable release of 3.5 μmol of NO during 12 hrs [41,44,45]. In a pilot study, developed in Landazuri, Santander, Colombia, a placebo-controlled clinical trial was conducted with 35 patients who presented 68 ulcers produced by *L. panamensis*. Using the NOP, a 65% improvement was observed in the treated ulcers, with only a 25% improvement in the placebo group (p = 0.001). In this pilot study the unique adverse event described was pruritus in the area where the patch was applied (unpublished data). Taking into account the wide distribution of CL, the changes in its form of transmission and the difficulty related with the availability of medication, this study proposes to investigate whether the NO donor transdermal patch, produced by electrospinning is, at least, as effective as the meglumine antimoniate for the treatment of CL, with less adverse events and a lower cost, constituting therefore an effective therapeutic alternative. In case that the effectiveness of the NOP is demonstrated in this study, a novel and safe therapeutic alternative of easy access and higher adherence for one of the most important public health problems in our country will be made available.

### Objectives

#### General objective

To evaluate the effectiveness and safety of NOP in the treatment of CL compared with meglumine antimoniate (Glucantime^®^).

#### Specific objectives

1. To evaluate the healing rate of CL ulcers using a NOP compared with the plan of treatment with meglumine antimoniate recommended by the health ministry.

2. To identify adverse events associated with the application of NOP and compare them with the ones produced by the treatment with meglumine antimoniate.

3. To identify and compare the recidivisms that may occur with both NOP and meglumine antimoniate.

4. To advance in the search of a therapeutic alternative for CL in Colombia.

### Design

Double blind, randomized, double-masked, placebo-controlled clinical trial, comparing nitric oxide releasing patches with meglumine antimoniate.

### Sample size

The sample was calculated according to the arccosine formula using a power of 80% and a type 1 error of 0.05%. Assigning a successful rate of 85% for meglumine antimoniate and 75% for NOP, 558 patients will be needed. After adjustment for a loss rate of 5%, the total of patients that must be recruited is 620 (310 patients per treatment group).

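### The sample-size paragraph does not reproduce: alpha is printed as 0.05%, the named formula does not give 558, and 620 matches a 10% loss, not the stated 5%

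*Protocol article*

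**What the plan says.** The whole calculation stands in the Sample size section of the protocol article.

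- Method: "The sample was calculated according to the arccosine formula".
- Error rates: "using a power of 80% and a type 1 error of 0.05", with a percent sign printed directly after the 0.05. Sidedness is not given.
- Rates and result: "Assigning a successful rate of 85% for meglumine antimoniate and 75% for NOP, 558 patients will be needed".
- Loss: "After adjustment for a loss rate of 5%, the total of patients that must be recruited is 620", which is broken down as "310 patients per treatment group".

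The abstract repeats 620 as the size of the trial. The Data analysis phase section schedules two interim analyses, at 35% and 70% of the calculated sample. It does not say whether that means 558 or 620.

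**The concern.** The paragraph is a chain: alpha, power and the two success rates lead to an evaluable number, and the loss rate leads from there to the recruitment target. None of its links can be reproduced from the printed inputs. The loss step fails by simple division. The printed alpha is a hundredth of the usual level and is incompatible with the printed sample size. At the usual level, the named formula gives a smaller number than the one stated.

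These are the figures by which anyone judges whether the trial is large enough and how much attrition it can bear. As written, a reader cannot tell whether 5% or 10% loss was planned for, or whether the design has the stated 80% power or something else. Loss matters here, with 20 days of daily treatment visits and follow-up to day 180. The interim looks inherit the ambiguity.

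**Working it through.** **Inputs (Sample size section).** Success 85% and 75%; power 80%; alpha printed as 0.05%; equal arms (310 each); loss 5%; stated totals 558 (279 per arm) and 620. Sidedness is not stated, so both were tried.

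**Step 1: effect size on the angular scale.** Arccosine and arcsine give the same absolute difference.

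h = 2·asin(√0.85) − 2·asin(√0.75) = 2.3462 − 2.0944 = 0.2518, so h² = 0.0634.

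**Step 2: attempt to reproduce 558.** Per arm, n = 2·(z_alpha + z_power)² / h², with z_power = 0.8416.

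- Alpha 5% two-sided: 2·(1.960 + 0.8416)² / 0.0634 = 247.6, so 248 per arm and **496** in total.
- Alpha 0.05% two-sided, as printed: 2·(3.481 + 0.8416)² / 0.0634 = 589.3, so 590 per arm and **1,180** in total. One-sided it is 538.6, so 539 per arm and 1,078 in total.

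Other common variants at 80% power:

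| Variant | Total |
|---|---|
| Angular, 5% two-sided | 496 |
| Unpooled normal approximation, 5% two-sided | 496 |
| Pooled normal approximation, 5% two-sided | 500 |
| Angular with continuity correction, 5% two-sided | 536 |
| Pooled with continuity correction, 5% two-sided | 540 |
| Fisher's exact test, 5% two-sided (80% reached between 265 and 270 per arm) | about 530 to 540 |
| The normal-approximation variants, 5% one-sided | 390 to 434 |

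None gives 558. The nearest, 540, is 18 short, and the named formula without correction is 558 − 496 = 62 short. Numbers near 558 appear only if an input is changed to one the plan does not state. For example, 85% power two-sided gives 568, and 90% power at 5% one-sided gives 542.

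**Step 3: power that the stated numbers deliver.** Power = Φ(h·√(n/2) − z_alpha), with n per arm.

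| Evaluable total | n per arm | h·√(n/2) | Power, alpha 5% two-sided | Power, alpha 0.05% two-sided |
|---|---|---|---|---|
| 558 | 279 | 2.974 | 84.5% | 31% |
| 589 (620 × 0.95) | 294.5 | 3.056 | 86% | 34% |
| 620 | 310 | 3.135 | 88% | not needed |

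**Step 4: the loss adjustment.**

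- 558 / (1 − 0.05) = 587.4, so 588.
- 558 × 1.05 = 585.9, so 586 (the common shortcut).
- 558 / (1 − 0.10) = 620.0 exactly.

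The implied loss rate is 1 − 558/620 = 10.0%. The target is 620 − 588 = 32 patients above what a 5% loss requires. Starting from the formula's own 496, a 5% loss gives 496/0.95 = 523 and a 10% loss gives 496/0.90 = 552.

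**Step 5: effect on the interim looks.** 35% and 70% of 558 are 195 and 391 patients; of 620 they are 217 and 434.

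**The case against.** Four points can be made for the plan.

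*The alpha is only a misprint.* The percent sign is almost certainly stray, because the Data analysis phase section uses ordinary 95% confidence intervals. The 31% and 34% power figures then describe no trial that anyone intended. This is fair: they show that the printed alpha cannot be the one used, not that power has collapsed. The printed value is still wrong by a factor of 100.

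*The totals may have a hidden logic.* 496/0.80 = 620 exactly, and the steps are equal: 558 − 496 = 62 and 620 − 558 = 62, each 10% of 620. So 558 may be an intermediate step in an inflation that the article does not describe. A condensed article may also leave out sidedness, a continuity correction or an allowance for the interim looks. This cannot be ruled out, and for that reason 558 is best called untraceable rather than miscalculated. But the route needs a 20% allowance that appears nowhere, and it contradicts the 5% that is printed.

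*The error is on the safe side.* At 5% two-sided, power for 85% versus 75% stays above 80% whether loss from 620 is 5% or 10%. Even a 20% loss leaves 620 × 0.80 = 496, which is enough. This stands, and it limits the consequence to traceability and possible over-recruitment.

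*The target is clear.* The abstract and the Sample size section agree on 620. That is true, but the reason given for 620 is not valid. Nor can the mismatch be put down to condensation, because the article itself prints the figures that disagree.

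**Conclusion.** The concern holds in all three parts, with differing firmness.

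- **Loss rate: certain.** It is pure arithmetic. 5% gives 588 and 620 needs 10%, a gap of 32 patients.
- **Alpha: certain as printed.** At 0.05% the design would need about 1,180 patients two-sided. That 5% was meant is an inference, though a strong one.
- **558: not obtainable from the stated inputs by any of the variants tried.** The named formula at 5% two-sided gives 496, and 558 gives about 84% power, not 80%. An undescribed inflation may explain the difference.

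If alpha is 5% two-sided and the success rates are 85% and 75%, the trial is larger than its own inputs require, so the defect does not threaten power for that difference. It must still be corrected, because alpha, power, evaluable number and tolerable loss are stated design figures and as written they contradict one another.

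**What to change.** Rewrite the Sample size paragraph so that each figure follows from the one before.

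1. Give the type 1 error as 5% (0.05) and say that it is two-sided, if that is what was used.
2. Name the formula variant, including any continuity correction.
3. Explain the step from 496 to 558. If an inflation was applied, name it and give its size. If none was, state that 558 evaluable patients give about 84% power by the angular formula.
4. Make loss and target agree: either 10% loss with 620 (310 per arm), or 5% loss with 588 (294 per arm).
5. In the Data analysis phase section, say whether the 35% and 70% looks refer to 558 or to 620.

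If the primary comparison is recast as non-inferiority, replace this calculation with one based on the margin.

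The cost is one reworded paragraph and a clarifying phrase. No extra patients are needed, and the target could fall.

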### Population

The population will be composed from two regions of Colombia. The first one is an endemic zone in Santander, Colombia, located between the Magdalena Valley and the East Mountain Range, which includes the municipalities of Landazuri, El Carmen, San Vicente, El Playon and Rionegro. The second region is an endemic zone in North Tolima, which includes the municipalities of Chaparral, San Antonio, Libano, Falan, Palocabildo and Mariquita.

### Selection of the patients

#### Inclusion criteria

1. Men and women between 18 and 50 years old

2. Cutaneous ulcers of more than two weeks of evolution

3. Positive parasitological diagnosis for CL

4. Patients that voluntarily accept to participate in the study and sign the informed consent.

5. Disposition to attend all the visits punctually (initial, treatment and follow-up)

6. Acceptation of not using any other treatment for CL while in the study

#### Exclusion criteria

1. Pregnant women

2. Presence of any condition or disease that compromises the patient immunologically (ie. diabetes, cancer, etc.) or, any other, that, based on the judgment of the researcher, could alter the course of CL.

3. Diffuse CL or more than five active lesions.

4. Mucocutaneous leishmaniasis (no lesion must be located less than 2 cm from the nasal, uro-genital, and/or anal mucous membranes or from the edge of the lips).

5. Visceral leishmaniasis.

6. Complete or incomplete treatment with antimony compounds in the last three months.

7. Patients with history of hepatic, renal or cardiovascular disease.

8. Mentally or neurologically disabled patients that are considered not fit to approve their participation in the study.

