### Screening visit

During this visit a complete clinical history will be elaborated and data about antecedents of leishmaniasis obtained (administered treatment, localization, number of lesions, etc). A full medical evaluation will be realized based on universally accepted techniques. The inclusion/exclusion criteria will be applied and the selected candidates informed about the study after which they will sign an informed consent. For those subjects with ulcers of more than two weeks of evolution without parasitological diagnosis a direct test will be performed by the parasitologist. If the first direct test is negative, it will be repeated up to three times; after which, in case of negative results, a biopsy will be performed. In case leishmaniasis is not confirmed the patient will be remitted to the original health center.

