### Follow-up visits

This phase will last 10 months. During the follow-up, the patients will be seen by the research group in 4 opportunities. The first visit will take place the day after the end of the treatment (day 21) in which new blood samples will be taken for biochemical determinations. The second, third and fourth visits will be realized on day 45, 90 and 180 respectively. During these visits the healing process of the ulcer, the presence of recidivisms and/or reinfection and the health of the participants will be assessed. The evolution of the ulcers will be photographically registered.

The maximum and minimum diameters of the ulcer will be measured using a graduated ruler, and the induration using the ballpoint pen technique. The ulcer and induration areas will be calculated separately, and then registered in the CRF. The evaluation of the clinical response will be based on the ulcer showing the least improvement.

1. Complete clinical response: Complete reepithelization of the ulcer and disappearance of the induration.

2. Clinical Improvement: Reduction of more than 50% of the ulcer and the induration areas in relation to the last clinical evaluation.

3. Absence of clinical response: Increase or reduction of less than 50% of the ulcer and the induration areas in relation to the last clinical evaluation.

4. Therapeutic failure:

a. Increase in the size of the ulcer by more than 50% in relation to the last clinical evaluation

b. Presence of the ulcer three months after the beginning of the treatment.

c. Reactivation: Appearance of a lesion on the edge or in the center of the scar, with positive parasitological diagnosis, after a period of complete reepithelization.

d. Affection of the mucous membranes: Presence of affections of the mucous membranes during the treatment, at the end of it or in the follow-up visits.

5. Reinfection: Activation of an ulcer in an area different from the original lesion.

For subjects whose treatment will have been considered a failure the code will be broken and they will be remitted to their original health center to look for other therapeutic approach.

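### The prior-treatment exclusion lets in patients whose current ulcer has already failed antimony, which tends to lower the comparator's success rate

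*Protocol article*

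**What the plan says.** The protocol article numbers its eligibility criteria, and exclusion 6 is the only one that looks back at earlier treatment: "Complete or incomplete treatment with antimony compounds in the last three months". The other criteria that might bear on the point do not close the gap:

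- Inclusion 6 looks forward only: "Acceptation of not using any other treatment for CL while in the study".
- Exclusion 2 concerns illness: "Presence of any condition or disease that compromises the patient immunologically". Its researcher-judgment clause continues that list of conditions and does not mention earlier drugs.
- Inclusion 2 sets a minimum ulcer age and no maximum: "Cutaneous ulcers of more than two weeks of evolution".
- Inclusion 3 requires "Positive parasitological diagnosis for CL".

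Under Follow-up visits, one definition of therapeutic failure is "Presence of the ulcer three months after the beginning of the treatment". Under Screening visit, the history includes "data about antecedents of leishmaniasis obtained (administered treatment, localization, number of lesions, etc", with no eligibility rule attached to the treatment recorded. The block randomisation in the Logistic phase section names no stratification by earlier treatment.

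**The concern.** A patient who took antimony before the trial and still has an open, parasite-positive ulcer more than three months later has failed the comparator by the protocol's own definition. Nothing bars that patient from being randomised to it again. Such patients are balanced between arms, but the effect need not be. In the antimony arm they receive the drug that did not work for them. In the patch arm they receive a treatment that very few people have ever had.

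The Background section sets out to show that the patch is at least as effective as antimony. A lower comparator rate narrows the difference and so favours that conclusion. It also undercuts the 85% planning rate in the Sample size section.

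A second, lesser gap is that exclusion 6 names antimony only. The Background also mentions amphotericin B and pentamidine as second-line drugs, and describes newer treatments "using oral agents such as mefloquine, itraconazole, miltefosine, paromomycin, ketoconazole, allopurinol and dapsone". A patient who has just finished one of these is not excluded, so healing begun by that drug could be counted for either arm.

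**Working it through.** **Timing.** Take three months as 90 days and assume the earlier antimony course lasted 20 days, as in this trial. Failure is established at about day 90 from the start of that course. Exclusion 6 lapses 90 days after its end, at about day 20 + 90 = 110. The patient becomes eligible roughly 20 days after meeting the failure definition.

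**Planning figures.** The Sample size section assumes 85% success on antimony and 75% on the patch, a gap of 10 points.

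**Effect on the antimony arm.** Let f be the share of enrolled patients who are earlier antimony failures and s their success rate on repeat antimony. The documents give neither, so both are assumptions. Then

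antimony rate = 0.85 × (1 − f) + s × f.

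With the patch held at 75% (also an assumption):

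| f | s | Antimony rate | Gap (points) |
|---|---|---|---|
| 0 | – | 85.0% | 10.0 |
| 5% | 70% | 0.8075 + 0.0350 = 84.25% | 9.25 |
| 5% | 50% | 0.8075 + 0.0250 = 83.25% | 8.25 |
| 20% | 70% | 0.6800 + 0.1400 = 82.0% | 7.0 |
| 20% | 50% | 0.6800 + 0.1000 = 78.0% | 3.0 |

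**If the patch is affected too.** Suppose these ulcers also do worse on the patch, by the same 0.85 − s. The patch rate becomes 0.75 − f × (0.85 − s), both arms fall together, and the gap stays at 10 points for every f and s.

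**How large could f be?** The Background cites a cure rate of about 85%, so about 15% of treated patients fail. If every one returned, they would make up 0.15 / 1.15 = 13% of presenters. At f = 13% the gap is 8.05 points (s = 70%) or 5.45 points (s = 50%). This is a rough upper guide, because it takes every failure to return and be eligible.

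**Power to detect a difference.** Take 558 / 2 = 279 patients per arm and a two-sided 5% test. That level is an assumption, because the printed type 1 error is 0.05%. With p̄ the mean of the two rates, power = Φ{[d√n − 1.96√(2p̄(1−p̄))] / √(p₁(1−p₁) + p₂(1−p₂))}. With the patch at 75%:

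- f = 0: gap 10 points, power 84%.
- f = 10%, s = 60%: antimony 0.765 + 0.060 = 82.5%, gap 7.5 points, power 58%.
- f = 20%, s = 60%: antimony 0.680 + 0.120 = 80.0%, gap 5 points, power 29%.

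**Other recent drugs.** Suppose a share g succeeds with probability 0.9 to 1.0 in either arm because of an earlier drug. The gap is then (1 − g) × 10 points: 9 at g = 10% and 8 at g = 20%. Both arms rise, so this dilutes the difference and favours neither treatment.

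**The case against.** Randomisation balances treatment history in expectation, so the comparison is valid for whoever is enrolled. On that view the issue is whom the result describes. The three-month window looks deliberate and includes incomplete courses, earlier treatment is recorded at screening, and the Data analysis phase section allows logistic regression if required. All of this is fair. It does not change the fact that one arm repeats a drug some patients have already failed, or that the direction favours the conclusion sought.

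A reader might infer that the imbalance is complete because nobody has had the patch before. The documents contradict this. The Background reports a placebo-controlled pilot of the patch in 35 patients in Landazuri, which the Population section lists as a recruiting municipality. The number is small, but earlier patch users are eligible too and the fix should cover them.

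A reader might also infer that a known bias has been shown. The documents support only a direction. The share of earlier failures is limited by the 18–50 age range, the required positive parasitology and the Background's statement that ulcers heal spontaneously within three months to a year. The 20% scenario exceeds even the 13% guide. The studies behind the 85% may already include previously treated patients.

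On other recent drugs, the objection largely stands. The Background describes amphotericin B and pentamidine as costly and hard to obtain, and finds too little evidence that the oral agents work. Required parasitology limits carry-over further. That protection is partial, because the Screening visit text describes a direct test for those without a diagnosis, so an older positive result might be accepted, although Table 1 marks the test at screening without that qualification.

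**Conclusion.** The point stands as a gap in exclusion 6 with a probable direction and an unknown size. Patients whose active ulcer failed antimony by the protocol's own three-month rule can be randomised to antimony again. This tends to lower the comparator's rate and favour a finding that the patch is as effective.

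With f of 5–20%, s of 50–70% and the patch unaffected, the planned 10-point gap becomes about 9.3 to 3 points. At the mild end the change is under one point, and if these ulcers do equally worse on the patch there is none. All three inputs are assumptions.

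The silence on other anti-leishmanial drugs is secondary. Reading it as a bias towards one arm would go too far: any carry-over is balanced by randomisation, is probably small, and only dilutes the difference.

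**What to change.** Reword exclusion 6 to exclude:

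- (a) any anti-leishmanial treatment, complete or incomplete, in the last three months; and
- (b) any previous treatment of a currently active lesion with either study treatment, antimony or the nitric oxide patch, at any time.

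The screening history already asks about earlier treatment, so little or no new data collection is needed. If such patients are already enrolled, add a sensitivity analysis of treatment success without them, identified from that history.

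The cost is an amendment to one criterion, a few lost screenings, and a conclusion limited to lesions not previously treated with either study treatment.
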